### Blinding

This study implements a single blind design by completely separating treatment and assessment.

Therapists will not be involved in assessing the treatment outcome. Raters will not be allowed to hold treatment sessions. Patients will be informed about their treatment allocation by the therapist but not by the raters. Only therapists will receive information about group allocation. Discussions about study patients are not allowed between raters and therapists. These principles were part of the staff training.

At the beginning of every visit, the raters will instruct the patient not to reveal their treatment condition and not to talk about details of their treatment. The raters will have to complete a "blindness protocol" after each visit. Any unintentional disclosure of the treatment condition will be documented. Further, the raters are asked to guess the study condition of the patient after each assessment. Among all documented guesses the rate of correct guesses should not be significantly different from chance (i.e. 50%).

In order to avoid any bias in data analyses data will be primarily analysed by the intention-to-treat principle. Further, statistical analyses will be conducted by an independent statistician of the Institute for Medical Biometry (IMB). The statistician is not involved in randomisation. The group variable (treatment allocation) will not be included until all data checks are completed. Even in case of severe adverse events no unblinding of raters will be necessary. In these cases therapists will start the appropriate crisis management strategies. If the rater is the first staff member to detect an adverse event he will give notice to the therapist who will implement all appropriate measures.

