**Figure 2 F2:**
[figure not shown]
**Informed consent and baseline examination (T0)**.

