### Randomization

All patients who give consent for participation and who fulfil the inclusion criteria will be randomized. Randomisation will be requested by the staff member responsible for recruitment and clinical interviews from CenTrial.

In return, CenTrial will send an answer form to the study therapist who is not involved in assessing outcome of the study. This form will include a randomisation number. In every centre closed envelopes with printed randomisation numbers on it are available. For every randomisation number the corresponding code for the therapy group of the randomisation list will be found in inside the envelopes. The therapist will open the envelope and will find the treatment condition to be conducted in this patient. The therapist then gives the information about treatment allocation to the patient. Staff responsible for recruitment and symptom ratings is not allowed to receive information about the group allocation.

As part of the efforts of quality assurance the correctness of the randomisation procedure in each patient will be monitored at the regular on-site visits.

The allocation sequence will be generated by the Institute for Medical Biometry (IMB) applying a permuted block design with random blocks stratified by study centre and medication compliance (favourable vs. unfavourable). The blocks should provide comparable numbers of patients in both conditions at any time in the course of the study. The block size will be concealed until the primary endpoint will be analysed. Throughout the study, the randomisation will be conducted by CenTrial in order to keep the data management and the statistician blind against the study condition as long as the data bank is open. The randomisation list remains with CenTrial for the whole duration of the study. Thus, randomisation will be conducted without any influence of the principal investigators, raters or therapists.

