***Efficacy***											

PANSS [22]	x	x	x	x	x	x	x	x	x	x	x

PSYRATS [28]	x	x	x	x	x	x	x	x	x	x	x

GAF and Social Status	x	x	x	x	x	x	x	x	x	x	x

Blindness Protocol	x	x	x	x	x	x	x	x	x	x	x

CSSRI^3 ^[61]	x		x		x		x	x	x	x	x

EQ-5D [64]	x		x		x		x	x	x	x	x

SUMD [30]	x						x		x		x

AMDP-psychosis items^2 ^[29]	x						x		x		x

Side effect rating scale [65]	x						x		x		

SCL-90-R [31]	x						x		x		x

FSKN [33]	x						x		x		x

Neuropsychological test battery	x						x				

^1^Suicide, Suicide attempts, ^2 ^items 33-58, ^3^includes assessment of medication and medication compliance; CDSS: Calgary Depression Scale for Schizophrenia; PANSS: Positive and Negative Syndrome Scale; PSYRATS: Psychotic Symptom Rating Scales; GAF: Global Assessment of Functioning; CSSRI: Client Sociodemographic and Service Receipt Inventory; EQ-5D: Euro Quality of Life - 5 Dimensions; SUMD: Scale to Assess Unawareness of Mental Disorder; SCL: Symptom Check List; FSKN: Frankfurter Selbstkonzeptskalen (Frankfurt Self-Concept Scales)

Treatment effects in the field of psychiatric disorders should always be assessed also from the viewpoint of the patient. However, a disorder of self evaluation is part of the positive syndrome which is the reason for choosing observer ratings as primary endpoint. On the other hand, the general rating of patients about their symptoms is important and is represented by the following secondary endpoint.

The Symptom Checklist [SCL-90-R; [31]] assesses subjectively felt impairments due to somatic and psychic symptoms within a frame of seven days. The SCL-90-R for example also assesses psychotic or depressive symptoms. Thus, self ratings of these symptom dimensions seem to be a sensible completion of symptom ratings. As CBT is supposed to reduce symptoms we hypothesize, that SCL-scores will be lower in CBT compared to ST at T9.

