On this background we aim to identify an effect size of more than .35 as significant given an anticipated drop out rate of 20%. An ES of .35 would be obtained if the PANSS Scores (Positive Syndrome) at the post treatment assessment were 12 for CBT and 14.5 for ST with a standard deviation of 7.14. An ES of less than .35 would be of limited clinical relevance.

This results in n = 130 per group for a power of 80% and a two-sided significance level of 5% (sample size calculated by nQuery 4.0, Panel MGT0). The confirmatory statistical analysis will be based on the intention-to-treat principle. Patients with missing PANSS-scores at T9 (post-treatment) will be included with the last observation carried forward (LOCF). In case of missing PANSS-scores at T9 the treatment effect will presumably be underestimated by using LOCF. To compensate for this underestimation the sample size should be adapted for drop out. Thus, we plan to include 330 patients (165 per study condition).

As assumptions about the real effect size cannot be based upon the literature we calculated different scenarios: in case of a lower effect size and/or drop out of more than 20% the statistical power will be reduced. For example, a reduced ES of 0.2 would result in a power of only 36% for the drop out of 20%. An increased drop out of 30%would reduce the power to 74% for the minimum ES of .35. On the other hand, a more favourable ES of 0.45 would increase the power to 85% for the maximum drop-out rate of 20%.

With a sample size of 330 individuals (165 each therapy group), ten assessments per patient, one primary analysis variable (therapy) and one covariable (center), the power should also be sufficient for a Mixed Model [42].

Table 3 gives an overview over the number of patients required in the different stages of the trial and the required effort for treatment and assessment. In order to successfully include 330 patients 6 study centers have been included which were committed to participate actively in this trial.

**Table 3 T3:** number of patients required in the different stages of the trial

	total	per center
required number of eligible patients (with 75% refusal)	1304	217
number of patients to be included (incl. 20% drop out)	330	55
number of patients to be analysed (ITT, LOCF)	330	55
number of patients to be analysed per protocol	260	44
treatment sessions (CBT and ST)	5530	922
number of visits	4620	770

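### The blinding check pools every rater guess against 50% and treats non-significance as success, so its result is hard to interpret in either direction

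*Protocol article*

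**What the plan says.** The Blinding section of the protocol article says that "the raters are asked to guess the study condition of the patient after each assessment". It then gives one standard for judging whether blinding worked: "Among all documented guesses the rate of correct guesses should not be significantly different from chance (i.e. 50"%). Unintentional disclosures are documented, but the standard does not treat guesses made after a disclosure differently.

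In Table 2 the row "Blindness Protocol" is marked in every column from T0 to F4. Figure 2 is titled "Informed consent and baseline examination (T0"), and the Randomization section places allocation after consent and the eligibility check: "All patients who give consent for participation and who fulfil the inclusion criteria will be randomized". A guess recorded at T0 would therefore precede any allocation.

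The section on the strengths of the design says only that the success of blinding will be assessed afterwards. The article names no test, significance level or variance method for this check.

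**The concern.** The standard fixes three things: the unit is every documented guess, the comparator is 50%, and success means failing to find a difference. Each causes difficulty.

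- **Repeated guesses.** A rater who has formed a view of a patient is likely to repeat it. Guesses from one patient are then correlated, and a test that ignores this rejects too often.
- **Mixed visits.** Early, late, follow-up and possibly pre-randomisation guesses go into one rate, together with guesses by raters who have been told the allocation. Unblinding at a few visits can be averaged away, and a few known disclosures can move the overall rate.
- **Success by non-significance.** Failing to reject 50% does not show that the rate is close to 50%.

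The primary endpoint is an observer-rated PANSS score, and patients and therapists know the allocation. The article lists the assessment of blinding among the strengths of the design, so readers will use its result to judge how far the ratings can be trusted.

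**Working it through.** **Inputs from the article.** Sample size: "Thus, we plan to include 330 patients (165 per study condition"). Visits in Table 2: T0, T1 to T9 and F1 to F4, so 1 + 9 + 4 = 14 per patient, of which 10 fall by T9 and 9 are post-baseline by T9. Expected drop-out is 20%.

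**Assumptions.** Two-sided 5% level for this check (the article states that level for the primary endpoint only). Within-patient correlation (ICC) of guesses 0.1 to 0.5. Pooled guesses tested as independent.

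**Step 1: reproduce the plan's count.** 330 × 14 = 4620, which matches the number of visits in Table 3. By T9 the count is 330 × 10 = 3300, or 330 × 9 = 2970 without T0.

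**Step 2: false alarms when raters are truly blind.** With m guesses per patient, the design effect is DE = 1 + (m − 1) × ICC. The actual error rate of a nominal 5% test is 2 × [1 − Φ(1.96/√DE)].

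| ICC | DE, m = 9 | m = 9 (T1–T9) | m = 10 (T0–T9) | m = 14 (T0–F4) |
|---|---|---|---|---|
| 0 | 1.0 | 5% | 5% | 5% |
| 0.1 | 1.8 | 14% | 16% | 20% |
| 0.3 | 3.4 | 29% | 31% | 38% |
| 0.5 | 5.0 | 38% | 40% | 47% |

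A simulation (4000 runs, 165 per arm, beta-binomial guesses independent of arm) agrees. At ICC 0.1, 0.3 and 0.5 it gave 15%, 31% and 39% for m = 10, and 18%, 37% and 48% for m = 14.

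**Step 3: width of the acceptance range.** The unclustered limits around 50% are ±1.96 × √(0.25/N). That is ±1.80 points for N = 2970 and ±1.44 points for N = 4620. With the design effect at m = 9 they become ±3.32 points (ICC 0.3) and ±4.02 points (ICC 0.5).

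**Step 4: unblinding confined to one visit.** As an illustration, suppose 60% of guesses are correct at T9 and 50% at every other visit.
- T0 to T9: (9 × 0.50 + 0.60)/10 = 51.0%, unclustered z = 1.15.
- T0 to F4: (13 × 0.50 + 0.60)/14 = 50.7%, unclustered z = 0.97.
- T9 alone: z = 0.10/√(0.25/330) = 3.63, or 3.25 with 264 patients (20% drop-out).

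The pooled check passes while the T9 guesses depart clearly from chance.

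**Step 5: known disclosures.** As an illustration, suppose 5% of patients disclose at T2 and are guessed correctly from T2 to T9. That is 0.05 × 330 × 8 = 132 certain answers among 3300. The pooled rate is (132 + 0.5 × 3168)/3300 = 52.0%, with z = 0.02/√(0.25/3300) = 2.30. The unclustered check fails although every other guess is random.

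**Step 6: baseline guesses alone.** If the later rate is p, adding one T0 guess per patient gives ((m − 1)p + 0.5)/m. A rate of 55% becomes 54.5% (m = 10) or 54.6% (m = 14). A rate of 60% becomes 59.0% or 59.3%. The shift is no more than one point in these cases.

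**The case against.** The strongest reply is that the article states an expectation, not a test. A clustered test of the overall rate would fit its wording, and such detail is commonly left to an analysis plan or full protocol that is not shown. This stands. A reader might infer that the trial will treat the guesses as independent and so has a false-alarm rate of 29% to 38%. The article does not support that: it names no test, the level and the correlation are assumptions, and at an ICC of 0.1 the rate is about 14%. Inflation of this kind also errs towards flagging a problem, which is the cautious direction for a blinding check.

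A reader might also infer that baseline guesses seriously pull the rate towards 50%. They do not (step 6). That such guesses exist is itself inferred from the T0 mark in Table 2. The form is not shown, and the item may be left blank at that visit.

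Third, the actual protection lies in the separation of raters from therapists, the ban on discussing patients, staff training and the instruction to patients at each visit. The guess rate is a diagnostic, and no stated decision depends on it. This also stands, so it would be wrong to infer that the primary test or the blinding itself is compromised.

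None of this reaches the rest of the stated rule. A clustered variance would not undo the pooling over visits, separate out guesses after disclosure, or make non-significance evidence that blinding held.

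**Conclusion.** The point holds as a weakness in how blinding success is to be judged. Pooling all guesses, with non-significance as the goal, can signal failure or success for reasons unrelated to whether raters were blind when it mattered. The false-alarm rate is about 14%, 29% and 38% at ICC 0.1, 0.3 and 0.5, for nine post-baseline guesses per patient, and only if the guesses are tested as independent at a two-sided 5% level. Masking of unblinding at particular visits does not depend on that condition, but its size depends on the pattern; step 4 shows one constructed case. Baseline guesses are a minor matter of tidiness. The primary efficacy analysis is unaffected. What changes is how far the reported blinding result can be relied on, which justifies a correction of wording.

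**What to change.** Replace the sentence in the Blinding section with a rule along these lines:

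- Exclude any guesses recorded at T0.
- Report the correct-guess rate or a blinding index by arm and by visit, with two-sided 95% confidence intervals. Show both an early post-randomisation visit and T9. T9 is when the primary endpoint is rated, but guesses there may reflect improvement the rater has seen, so a high rate at T9 alone does not prove that blinding was broken.
- For any summary over visits, use a method that allows for repeated guesses per patient, and per rater.
- Show results with and without patients with a documented disclosure.
- Judge blinding from the estimate and its interval, and delete the non-significance criterion. With one guess per patient the interval is about ±5.4 points around 50% for 330 patients and ±6.0 for 264, which shows what the data can and cannot exclude.

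A repeat of the primary analysis without patients whose rater was unblinded before T9 is at most a supportive sensitivity analysis, because it selects on an event after randomisation.

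The cost is analysis wording only. Guesses and disclosures are already to be recorded at each visit, so no extra assessment or sample size is needed. The wording should be settled before the primary analysis, which the article schedules to start after T9 assessments are complete.

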### Cognitive behavioural therapy

CBT for the treatment of positive symptoms in psychotic disorders is based on general CBT principles. Participants are regarded as active, self responsible individuals. During all phases of the treatment patients are requested to actively participate in the treatment and to take responsibility for decisions how to proceed together with the therapist. The therapeutic process rests on the cooperation between patient and therapist. Whenever necessary, the therapist modifies his intervention in order to help the patient to engage in the therapeutic process.

Treatment is built on a case formulation: Patients and therapist will engage in developing a shared definition of the major problem of the patient. When providing information about psychosis therapists will use a normalising and non-stigmatising style of explanations. The formulation has to address (explicitly or implicitly) persistent positive symptoms. A shared formulation is thought to be a necessary prerequisite for a successful treatment. The specific problems to be addressed in CBT are delusions and hallucinations. The treatment is aimed at helping the patient cope with these symptoms. A major principle of CBT is to link behaviour, emotion and cognition in order to provide a detailed understanding of the patient's problems. Psychotic symptoms are understood as result of dysfunctional ways of perceiving and interpreting social situations. CBT aims at correcting the person's misperceptions, irrational beliefs and reasoning biases as well as at reducing the distress caused by symptoms and the improvement of social functioning. Participants engage in monitoring own thoughts, feelings and behaviours. They are encouraged to test alternative ways of coping with the target symptom. Strategies for the treatment of delusions and delusional processing of hallucinations are to review the information processing (perception bias, jumping to conclusions, attributional bias, theory of mind deficit), to engage in schema work in order to modify potentially delusion related self schemata, to plan activities for reality testing which will provide evidence for or against the delusional conviction, and to help patients reduce the disruption of life and daily activities caused by the delusions. Strategies to reduce hallucinations are to improve the patients coping strategies (e.g. systematic distraction strategies), and to identify and change social or internal stimuli related with increased hallucinatory experiences.

Major stages of CBT can be described as follows:

• Engagement (strategies to foster motivation for treatment participation)

• Assessment (regarding symptoms and social problems)

• Developing understanding of psychotic symptoms using a "normalising" style of providing information )

• Case formulation and treatment planning

• Specific techniques designed to address delusions and hallucinations

• Specific techniques designed to address dysfunctional beliefs and schemata

• Specific techniques designed to improve social functioning

(See Figure 4)

**Figure 4 F4:**
[figure not shown]
**Cognitive Behavioural Therapy - Overview**.

The CBT manual of the POSITIVE study is published in German language at the research network's homepage http://www.psychose-psychotherapieforschung.de

### Supportive Therapy

ST will be used as comparator in order to control for non-specific elements of therapeutic contact. Psychotherapy outcome is generally thought of as consisting of both specific and non-specific effects. Non-specific effects like emotional support, therapeutic attention, empathic listening, implementation of therapeutic optimism and others are the result of every successful therapeutic relationship. In contrast, therapeutic outcome, which is directly linked to specific and well-defined treatment strategies, is called specific effect. It is hypothesised that CBT produces specific and non-specific factors whereas ST should only result in non-specific factors. ST does not rely on specific theories or assumptions about the causes of positive symptoms in psychotic disorders. ST will focus on the patients' experiences and daily activities. The sessions will focus on neutral topics, such as hobbies, sports, and current affairs. Therapists will engage in listening to the patient, in being empathic, in helping the patient structure the available time and discussing problems in way friends would do. Thus, ST is thought as an active treatment with respect to the patient-therapist relationship and with respect to therapeutic commitment [21]. In the treatment of patients suffering from psychotic disorders these ingredients are viewed to be essential as it has been shown consistently that the social network of these patients is limited. To have at least one trustworthy person to talk to may be the most important ingredient in any kind of treatment. However, with respect to specific processes related to modification of psychotic beliefs, ST is not an active treatment. Strategies specifically designed to change misperceptions or reasoning biases are not part of ST.

Major aspects of ST will be:

• Engagement

• Assessment of social problems and interests of the patient

• Treatment planning

• Focus on housing, work, leisure time, hobbies, and events, as adequate.

Psychotic or affective symptoms will not directly be tackled in any way. (See Figure 5)

**Figure 5 F5:**
[figure not shown]
**Supportive Therapy - Overview**.

The ST manual of the POSITIVE study is also published at the research network's homepage http://www.psychose-psychotherapieforschung.de.

### Formal characteristics of study therapies

CBT and ST are individual outpatient treatments of 20 sessions over 9 months (7 sessions in the first seven weeks, followed by 13 fortnightly sessions)

CBT as well as ST will be conducted by specifically trained psychotherapists on the basis of a treatment manual. Each therapist conducts both the CBT and the ST treatment. In order to take responsibility as study psychotherapist, staff members have to have at least one year of clinical experience as clinical psychologist or resident in psychiatry. In addition, they have to be enrolled in formal training programs for cognitive behavioural therapy or have to have completed their formal training.

In the case of interruptions of the study therapies due to rehospitalisation of patients, holidays, other illnesses of patients, illness of therapists etc. the treatment will be continued as soon as possible. However, continuation is only possible within a time frame of 9 months after study inclusion. Thus, within 9 months after study inclusion interruptions of participation will not result in termination of the study treatment, exclusion from the study or a new screening. When continuing the treatment the remaining sessions will be scheduled on a weekly basis as long as necessary. Thus, even patients with longer interruptions will have the chance of getting a maximum of the 20 sessions. In each case, study therapies have to be terminated 9 months after study inclusion (primary endpoint).

### Primary Endpoint

The primary endpoint for the biometrical evaluation of the therapy is the Positive Score of the Positive and Negative Syndrome Scale (PANSS, [22-24]). This psychopathological rating scale represents a common standard rating used in a wide range of outcome studies in schizophrenia. It will be assessed 9 months after inclusion of the participant.

The PANSS positive score is defined by seven items of the PANSS (P1 - P7), all 7-point rated with higher scores representing increasing levels of psychopathology. It will be computed as the mean of these seven items in order to provide a score that is easy to interpret on the scale of a single item.

The German version of the PANSS was evaluated for interrater reliability by Müller et al. [25] and was used for the assessment of the primary endpoint by most of the studies of the German Research Network on Schizophrenia [26].

For the purpose of this trial PANSS is regarded as a validated assessment instrument for positive symptoms. No own validation studies on the PANSS will be conducted. Moreover, the normal distribution and other prerequisites for parametric analyses (e.g. interval scale type) of the PANSS positive-syndrome score will be assumed.

In order to ensure the interrater reliability of the rater responsible for patient assessments in this study, the raters will be trained for PANSS-rating. At the end of the training the interrater reliability between the raters will be assessed using videotaped interviews. Three videos will be assessed by all raters and the reliability will be statistically evaluated by the intraclass correlation coefficient (ICC). The reliability will be regarded as acceptable if the ICC of the PANSS-positive score will be .8 or higher. If the ICC is lower than .8 the rater training will be continued until the criterion is fulfilled. Assessment for reliability will be repeated in case of any change of raters.

During the course of the study the interrater reliability will be assessed regularly every year in order to analyse rater shift. It will be reported whether raters demonstrate a tendency of higher or lower ratings at the end of the study.

As persistent positive symptoms are chronic symptoms which change very slowly a two-year follow-up after completion of treatment will be conducted. The primary endpoint will be analysed also at the end of the follow-up period.

